## Abstract

**Background:**

In the Lake Victoria Basin of western Kenya, malaria remains highly endemic despite high coverage of interventions such as insecticide-impregnated long-lasting insecticidal nets (LLIN). The malaria-protective effect of LLINs is hampered by insecticide resistance in *Anopheles* vectors and its repurposing by the community. Ceiling nets and LLIN with synergist piperonyl butoxide (PBO-LLIN) are novel tools that can overcome the problems of behavioral variation of net use and metabolic resistance to insecticide, respectively. The two have been shown to reduce malaria prevalence when used independently. Integration of these two tools (i.e., ceiling nets made with PBO-LLIN or Olyset®Plus ceiling nets) appears promising in further reducing the malaria burden.

**Methods:**

A cluster-randomized controlled trial is designed to assess the effect of Olyset®Plus ceiling nets on reducing malaria prevalence in children on Mfangano Island in Homa Bay County, where malaria transmission is moderate. Olyset®Plus ceiling nets will be installed in 1315 residential structures. Malaria parasitological, entomological, and serological indicators will be measured for 12 months to compare the effectiveness of this new intervention against conventional LLIN in the control arm.

**Discussion:**

Wider adoption of Olyset®Plus ceiling nets to complement existing interventions may benefit other malaria-endemic counties and be incorporated as part of Kenya’s national malaria elimination strategy.

**Trial registration:**

UMIN Clinical Trials Registry UMIN000045079. Registered on 4 August 2021.

## Introduction

### Background and rationale {6a}

Vector control is a key component of malaria control programs worldwide. Among several vector control strategies, bed nets are the most widely adopted tool to prevent mosquito bites and malaria transmission. Insecticide-treated nets (ITN), especially long-lasting insecticidal nets (LLIN), are the single most important contributor to the remarkable reduction of malaria cases and deaths since the early 2000s [1, 2]. However, that trend has stalled since 2015. Malaria cases are even increasing in some countries [3], suggesting the need to optimize the use of existing tools, including LLIN, malaria rapid diagnostic tests (RDT), and artemisinin-based combination therapy (ACT), as well as the addition of novel tools and an update of current control combination strategies.

Repurposing and inconsistent uses of LLIN are widely observed where mass LLIN distribution has been implemented. These may act as key factors in reducing the impact of LLIN. For example, in the Lake Victoria region of Kenya, the repurposing of LLIN for fishing and protecting crops and livestock are well known [4, 5]. Sharing a single LLIN by more than two persons can also reduce its protective effect [6]. Furthermore, our previous study showed that schoolchildren, who are most vulnerable to malaria infection, tend to sleep in the living room without bed nets [7].

Additionally, several studies have demonstrated that house screening reduces the number of mosquitoes entering the structure and also protects those who do not use bed nets properly [6, 8]. Screens that cover the ceiling and the gap between the ceiling and the walls (ceiling nets) are especially effective since these gaps are the major entry points for mosquitoes into the house [9, 10], and mosquitoes habitually rest on walls or ceilings after a blood meal [11, 12]. Hence, ceiling nets with insecticide-treated material can kill infected mosquitoes and interrupt malaria transmission [13, 14]. Moreover, once installed, ceiling nets demand little to no input from users, unlike conventional bed nets that require setting before sleep and removing in the morning; hence, the impact may be less influenced by inconsistent human behaviors [15–17].

Resistance to pyrethroid insecticides in mosquitoes can undermine the current LLIN strategy. There are currently two main mechanisms of insecticide resistance in anopheline mosquitoes, target-site mutations in the pyrethroid receptor and metabolic resistance [18]. Metabolic resistance is caused by allelic and expression changes in cytochrome P450 enzymes that detoxify pyrethroids [19]. To combat this type of pyrethroid resistance, Olyset®Plus, an LLIN incorporating the insecticide synergist piperonyl butoxide (PBO), has been developed. PBO inhibits the enzymes that break down pyrethroids. Previous studies have demonstrated the increased insecticidal effect of Olyset®Plus when compared with the standard LLINs, even in areas where pyrethroid-resistant mosquitoes were widely reported [20–22].

Integration of ceiling nets and LLIN with PBO (Olyset®Plus ceiling nets) can address the major shortcomings of current LLIN and provide additional protection against malaria over individual adoption of either tool. However, a few malaria-endemic areas, including our study area, still have high malaria prevalence even after the wide and repeated distribution of LLIN to the community, suggesting that the current LLIN program is insufficient for combating residual malaria transmission. Olyset®Plus ceiling net has the potential as one of the updates of the current LLIN. Here, we designed a cluster randomized controlled trial to evaluate its protective efficacy in reducing malaria prevalence. The most vulnerable population to malaria is small children. However, young adults or adults are also an important population in malaria transmission since they can act as a reservoir of transmission as asymptomatic infections. Thus, the proposed study includes monitoring two target populations: school-age children (3 to 15 years old) and all age groups.

### Objectives {7}

The primary study objective is to determine the protective efficacy of Olyset®Plus ceiling nets in reducing malaria prevalence in children aged 3 to 15 years old, during a 12-month follow-up period.

The secondary objectives during a 12-month follow-up period are as follows: (1) to determine the total number of infections averted due to Olyset®Plus ceiling net by comparing the cumulative number of infections per person per year in cohort participants in the intervention and control arms; (2) to determine the protective efficacy of Olyset®Plus ceiling net in reducing anemia prevalence in children aged 3 to 15 years old; (3) to measure the impact of Olyset®Plus ceiling net on entomological parameters (anopheline mosquito density, composition, and malaria infection rate), (4) to measure the impact of the introduction of Olyset®Plus ceiling net on malaria preventive behavior, especially bed net usage after the 12 months of the intervention; and (5) to assess the acceptance of Olyset®Plus ceiling net within the community.

### Trial design {8}

The study is a cluster-randomized controlled trial with 10 clusters per arm (intervention and control), consisting of two cross-sectional school surveys after 6 months and 12 months of intervention and one cohort followed for 12 months in both arms. Each cluster is a health unit comprising approximately 100 households, including 500 individuals. Each health unit has an assigned community health volunteer (CHV) responsible for national health surveys and routine community health activities. This study also utilizes CHVs as messengers of study-related information and enumerators of the questionnaire surveys.

To evaluate the primary outcome, 150 schoolchildren will be recruited from each cluster. To evaluate the protective efficacy in reducing the cumulative incidence, 25 individuals will be recruited from each cluster and followed up for 12 months as a cohort. Residents of all age groups will be recruited to allow for the evaluation of the impact on asymptomatic and/or submicroscopic infections, which are also observed in adults. Cohort participants will be interviewed about their health conditions every 2 weeks by CHVs and are asked to provide a blood sample to monitor asymptomatic infection. The blood collection will be done by finger prick and venipuncture alternately. Five house structures in each cluster will be randomly selected and subjected to pyrethrum spray catches (PSC) for the entomological assessment. The mosquito sampling will be implemented 6 and 12 months after the intervention. Sampling will take place at the same structures at both time points.

## Methods: participants, interventions, and outcomes

### Study setting {9}

The study will be conducted on Mfangano Island in Homa Bay County, Kenya (Fig. 1). According to the most recent national census in 2019, the island has a land area of 66.2 km^2^ and a population of 24,123 distributed in 6085 households [23]. Luo and Suba are the major and minor ethnic groups on the island, respectively, with significant admixture between the two groups. The primary occupations of Mfangano residents include fishing in Lake Victoria and farming. Most compounds possess more than two house structures, and family dwell in each structure is referred to as a household. The main dwelling units are typically made of mud walls with metal sheet roofs, although units with walls made of iron sheets, concrete, or stones are also common [23].

**Fig. 1 Fig1:**
[figure not shown]
Map of Mfangano Island showing the locations of the 20 trial clusters

In general, the Lake Victoria region has two rainy periods per year, including the long rainy season from March to June and the short rainy season from October to November. However, irregular patterns have been observed in the last few years [24]. Malaria incidence peaks 1 to 2 months after the rainy season. The major vectors are *Anopheles gambiae* s.s., *An. arabiensis*, and *An. funestus* [25].

Mfangano has six public health facilities (three health centers and three dispensaries). The island is divided into 52 health units, each comprising 50 to 100 households. A CHV will monitor the health status of residents in each health unit. Under Homa Bay County government mandate, CHVs are to test suspected malaria cases by RDT and provide ACT treatments to confirmed positive cases. LLINs are distributed for free by the government every 3 years, and the most recent distribution in Homa Bay County began in March 2021.

### Eligibility criteria {10}

The inclusion criteria for the installation of the Olyset®Plus ceiling net are (1) residential structures housing at least one permanent resident aged 18 years or older in the household and (2) informed consent provided by at least one adult in the household. The exclusion criteria are (1) vacant dwelling structure (confirmed by at least two visits by CHVs) and (2) dwelling structure to be vacated or destroyed within the study period.

The inclusion criteria for cross-sectional malaria and anemia prevalence surveys in schools are (1) age between 3 and 15 years old, (2) living in the study area during the study period, and (3) informed consent being provided by the parent or legal guardian before each survey. The exclusion criterion is (1) having severe chronic illnesses.

The inclusion criteria for prospective cohorts are (1) living in the study area at the time of Olyset®Plus ceiling net installation, (2) having no plan to leave or stay outside the study area for an extended period (longer than 1 month) over the 12-month follow-up period, and (3) informed consent provided (if the participant is minor (less than 18 years old), informed consent has to be provided by the participant’s parent or guardian). The exclusion criteria are (1) severe chronic illnesses and (2) pregnancy at the time of Olyset®Plus ceiling net installation. Table 1 summarizes these criteria.

**Table 1 Tab1:** The inclusion and exclusion criteria for ceiling net installation, cross-sectional survey, and prospective cohort survey

Inclusion criteria	Exclusion criteria
**Ceiling net installation**	
At least one permanent resident aged 18 years or older in the household	Vacant dwelling structure (confirmed with at least two visits by CHVs)
Informed consent provided by at least one adult in the household	Dwelling structure to be vacated or destroyed within the study period
**Cross-sectional survey**	
Age between three and 15 years old	Severe chronic illnesses
Living in the study area during the study period	
Informed consent was provided by the parent or guardian before each survey	
**Prospective cohort survey**	
Living in the study area at the time of Olyset®Plus ceiling net installation	Severe chronic illnesses
No plan to leave or stay outside the study area for an extended period (longer than one month) over the 12-month follow-up period	Pregnancy
Informed consent provided (if the participant is a minor, informed consent must be provided by the participant’s parent or guardian)	

### Who will take informed consent? {26a}

Written informed consent will be obtained by the study team members fluent in the local languages (Luo), Kiswahili, and English and who fully understand the study protocol. After eligibility is confirmed, the study team members will present to the potential participant a document containing all relevant information about the study in Luo and English. If the participant cannot read, study information will be conveyed verbally by the study team members. The potential participant will have opportunities to ask any questions. Agreement to participate is sought only after the participant indicates an appropriate understanding of the study.

### Additional consent provisions for collection and use of participant data and biological specimens {26b}

The study information document for ceiling net installation contains the study overview. In addition, the documents for cross-sectional and cohort surveys contain details on collecting, storing, and using personal data and biological specimens during the study.

### Interventions

#### Explanation for the choice of comparators {6b}

In Kenya, LLIN is the most widely used malaria preventive measure. The Division of National Malaria Programme coordinates free LLIN distribution, and the county governments deliver LLINs to residents in all endemic counties every 3 years. The primary purpose of this trial is to demonstrate the superiority in malaria prevention of adding Olyset®Plus ceiling nets to the standard LLIN. Thus, in the control arm, no Olyset®Plus ceiling nets will be installed. Free LLIN distribution and use will be allowed in the control and intervention arms as the current best practice. As for the planning stage, there is no plan for new LLIN distribution during the study period.

#### Intervention description {11a}

In the intervention arm, Olyset®Plus ceiling nets will be installed in all dwelling units where residents sleep, free of charge to the households. All participants will be encouraged to continue to use LLINs, distributed by the Homa Bay County government.

Ceiling net installation teams consisting of experienced installers who have participated in the previous ceiling net trial [14], CHVs, and community volunteers from each health unit will schedule the installation time for each eligible household. The head (or another adult) of the eligible household will be informed at least 24 h prior to the scheduled installation time.

The ceiling net material is a rectangular sheet of Olyset®Plus net measuring 6 m × 8 m or 4 m × 6 m, depending on the size of the house [8]. The ceiling net has loops along the diagonals, allowing the net to be roped to the roof support beams. After tying the central loop to the center of the roof, all four sides of the net will be pulled taut, and the remaining loops will be tied to the roof support beams. The edges of the ceiling net are then pinned to the walls, screening the opening between the roof and the walls (Fig. 2).

**Fig. 2 Fig2:**
[figure not shown]
Scheme of the ceiling net and the process for the installation. **A** The rectangular LLIN sheet is reinforced along the edges and diagonals. Four loops sewn on each diagonal and one central loop sewn at the intersection of the diagonals enable the net to be tied with strings to the roof support beams and the center of the roof, respectively. **B** The central loop is tied to the center of the roof. **C** The net is pulled tight to avoid slack, and the rest of the loops are tied to the support beans. **D** The edges of the net are pinned to the top of the walls, and the gap between the walls and the roof is screened

#### Criteria for discontinuing or modifying allocated interventions {11b}

Since the ceiling net is semi-permanently installed, the intervention will be discontinued only when the participant specifically requests the removal of the ceiling net by the study team. We do not allow any crossover from the control arm to the intervention arm during the follow-up period. Those who migrate between the arms or emigrate from the study areas will be dropped from the study follow-up.

#### Strategies to improve adherence to interventions {11c}

Adherence to the intervention cohort in this study is defined as sleeping in houses with Olyset®Plus ceiling nets. Adherence is monitored indirectly by assessing the number of nights each participant spends outside their house during the bi-weekly interview. During each house visit, CHVs will visually inspect the condition of the ceiling nets. Any visible tear and damage to the ceiling net will be reported to the research team by the size and location of the damage.

#### Relevant concomitant care permitted or prohibited during the trial {11d}

There is no specific concomitant care prohibited during the trial. All participants in both arms will continue to receive and use free LLIN and have access to standard medical care, including malaria testing by RDT and treatment with ACT.

#### Provisions for post-trial care {30}

All participants will be under the normal healthcare system in the study setting. No perceived health risks for the intended population are expected with the intervention. Our plan of continuous cross-sectional malaria surveillance after the study period allows us to monitor further parasite transmission in the population.

### Outcomes {12}

The primary outcome of the study is malaria prevalence by microscopy in schoolchildren (3 to 15 years old) 12 months after Olyset®Plus ceiling net installation. The secondary outcomes are (1) malaria prevalence by PCR in schoolchildren at 6 and 12 months post-installation; (2) cumulative malaria incidence in the prospective cohort for 12 months post-installation; (3) anemia prevalence in schoolchildren at 6 and 12 months post-installation; (4) prevalence and level of antibodies (IgG) against *Anopheles* salivary proteins gSG6 and cE5 in the prospective cohort at 6 and 12 months post-installation, as a measure of exposure to mosquito bites; (5) anopheline mosquito density, species composition, and sporozoite infection prevalence at 6 and 12 months post-installation; (6) the percentage of cohort participants who sleep under the bed net at 6 and 12 months post-installation; and (7) perception of the Olyset®Plus ceiling nets among community members.

#### Participant timeline {13}

The study flowchart and sampling timeline are presented in Table 2.

**Table 2 Tab2:** The study flowchart

		Study period																
Time point (weeks)		− 8	0	2	4	6	8	10	12	14	16	18	20	22	24	…	48	50
Enrollment	Eligibility screen	X																
	Informed consent	X																
	Allocation		X															
Interventions	Install the ceiling net		X															
Assessments (cohort)	Questionnaire survey by CHVs		X	X	X	X	X	X	X	X	X	X	X	X	X	…	X	
	Venous blood sampling by a lab tech				X				X				X			…		
	Capillary blood sampling by a lab tech		X				X				X				X	…	X	
	Passive case detection			X	X	X	X	X	X	X	X	X	X	X	X	…	X	
	Qualitative survey																	X
Assessments (cross-sectional)	School malaria survey		X														X	

#### Sample size {14}

Parasite prevalence by microscopy among schoolchildren on Mfangano Island is approximately 20%, based on our previous study [26]. To detect the expected effect of 60% parasite prevalence reduction (to a prevalence of 8%) relative to control, with a power of 0.8, two-sided type 1 error of 5%, an intraclass correlation coefficient (ICC) for clusters of 0.063 (estimated based on our previous school study by assuming each school as a cluster), and average cluster size 150 (number of schoolchildren), the required number of clusters is 10 (or 1500 children) per arm using Stata/MP16.1. Based on the 2019 national census, children 3 to 15 years old account for 40.3% of the total population in Homa Bay County. The study requires a total population (all ages) of 7444 people or 1880 households (mean of 3.96 persons per household on Mfangano). By assuming a 3% dropout per month, we plan to enroll 1315 households for the intervention arm.

For the longitudinal cohort, we estimate the infection incidence on Mfangano Island as approximately 2.0 per person-year based on the data on Kenya Health Information System (KHIS). To detect the expected effect of a 40% reduction (1.2 per person-year), with a power of 0.8, two-side type 1 error of 5%, and an average cluster size of 25 individuals, the required number of clusters is 7 (or 350 individuals) per arm based on Eq. 7.3 on reference [27]. Assuming 3% of cohort participants will drop out per month, we plan to enroll 490 individuals in the cohort.

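### Cohort sample size: 7 clusters of 25 is 175 individuals per arm (350 in total), not 350 per arm, and the between-cluster variation behind the 7 is not stated

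*Protocol article*

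**What the plan says.** All of the cohort calculation is in the Protocol article, Sample size {14}, second paragraph.

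- Control rate: "we estimate the infection incidence on Mfangano Island as approximately 2.0 per person-year", taken from routine health information data.
- Effect: "To detect the expected effect of a 40% reduction (1.2 per person-year").
- Error rates and cluster size: "with a power of 0.8, two-side type 1 error of 5%, and an average cluster size of 25 individuals".
- Result: "the required number of clusters is 7 (or 350 individuals) per arm based on Eq. 7.3 on reference [27]".
- Enrolment: "Assuming 3% of cohort participants will drop out per month, we plan to enroll 490 individuals in the cohort".

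No ICC or coefficient of variation is given for the cohort. The primary calculation, one paragraph earlier, does give one: "an intraclass correlation coefficient (ICC) for clusters of 0.063", at a control prevalence of about 20%, estimated with schools treated as the clusters.

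Trial design {8} sets 10 health-unit clusters per arm and says that "25 individuals will be recruited from each cluster and followed up for 12 months as a cohort".

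**The concern.** There are two separate matters.

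First, the individuals do not match the clusters. With 25 per cluster, 7 clusters cannot hold 350 people. The primary calculation uses the same form of words correctly: 10 clusters of 150 is 1500 per arm. A reader who takes 350 per arm at face value needs 700 before dropout and would conclude that a cohort of 490 is far too small.

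Second, the power of a cluster trial depends heavily on how much the true rates differ between clusters. Without that input, the 7 clusters and the 80% power cannot be checked. If the value used was optimistic, a null cohort result could be read as stronger evidence of no effect than it is. The cohort carries the first-listed secondary objective (Objectives {7}), and the Discussion presents infection incidence by active case detection as what is new about the trial.

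**Working it through.** **1. Individuals per arm**

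- 7 × 25 = 175 per arm; 2 × 175 = 350 in total.
- Enrolment from 350 in total: 350 / 0.97^11 = 489.3, which matches the stated 490.
- Enrolment from 350 per arm: 700 / 0.97^11 = 978.6, which does not match.
- The household figure uses the same factor: 1880 / 2 = 940 per arm, and 940 / 0.97^11 = 1314.1, against 1315 stated.

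So 350 is the two-arm total.

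**2. Reproducing the 7 clusters**

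Assumption: the cited Eq. 7.3 is the standard unmatched formula for rates,

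c = 1 + (z_α/2 + z_β)² × [(λ0 + λ1)/y + k²(λ0² + λ1²)] / (λ0 − λ1)²

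Inputs: λ0 = 2.0, λ1 = 1.2, y = 25 person-years per cluster, (1.960 + 0.842)² = 7.849. Then (λ0 + λ1)/y = 0.128, λ0² + λ1² = 5.44 and (λ0 − λ1)² = 0.64.

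- k = 0.25: c = 1 + 7.849 × (0.128 + 0.340)/0.64 = 6.74, rounded up to 7.
- The result rounds up to 7 only for k between about 0.227 and 0.258.
- Other forms of the calculation (no added 1, 50 person-years per cluster, person-years reduced for dropout) move the upper limit only to between 0.237 and 0.285.

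The stated 7 therefore points to k of about 0.25.

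**3. Comparison with the primary calculation**

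A between-cluster variance of ICC × p(1 − p) gives k = √[ICC(1 − p)/p].

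- At p = 0.20: k = √(0.063 × 0.8/0.2) = 0.50.
- At k = 0.50: c = 1 + 7.849 × (0.128 + 1.360)/0.64 = 19.25, i.e. 20 clusters per arm.

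**4. Power of the planned design (10 clusters of 25 per arm)**

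Power = Φ{√[(10 − 1) × 0.64/(0.128 + 5.44k²)] − 1.96}

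| k | Power, y = 25 | Power, y = 20.9 (3% monthly dropout) |
|---|---|---|
| 0.25 | 0.94 | 0.93 |
| 0.35 | 0.77 | 0.76 |
| 0.40 | 0.67 | 0.66 |
| 0.50 | 0.50 | 0.50 |

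The largest k with 80% power is √{[(9 × 0.64/7.849) − 0.128]/5.44} = 0.33.

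**The case against.** **The label changes nothing in the design.** This stands. The next sentence enrols 490 for the whole cohort, and Trial design {8} recruits 2 × 10 × 25 = 500. A reader might infer from 350 per arm that the cohort is enrolled at half its required size; the document's own figures rule that out. The stated number is still wrong.

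**The two calculations need not share one heterogeneity.** This also stands. A reader might infer that the cohort calculation contradicts the primary one and that true power is about 50%. The documents do not establish either. The ICC was estimated with schools as clusters, whereas the trial's clusters are health units. It also describes a positive smear at one time point in children, whereas the cohort outcome is a rate over 12 months at all ages. In addition, the cohort k is back-calculated under an assumed form of an equation that the document only cites. A k near 0.25 is possible; it is just not stated or justified.

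**The 7-cluster limit is not the trial's limit.** Correct. A reader might infer that 80% power is lost once k exceeds about 0.26, half the converted value. That applies to 7 clusters. The planned 10 clusters per arm keep 80% power up to k of about 0.33, two-thirds of the converted value.

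**The dropout allowance.** A reader might also infer an error because 490 reflects 11 months of loss, and 12 months would give 350/0.97^12 = 504.4, or 505. Table 2 places the last scheduled cohort blood sample at week 48, about 11 months, and the design already recruits 500. This is not an error.

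**The cohort's small size is acknowledged.** The Discussion does call the cohort small, but it draws a conclusion about generalisability, not about power.

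**Conclusion.** The per-arm cohort size is misstated: it should be 175, with 350 as the total. This is certain from the section's own figures and needs no assumption. It is a labelling error that leaves enrolment unaffected.

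The power statement cannot be checked as written, because the between-cluster variation is missing although the primary calculation in the same section gives its own. Under the assumed formula, the 7 clusters imply k of about 0.25. The only between-cluster figure in the document converts to about 0.50. That gap is a reason to show sensitivity; it is not a proven inconsistency. For the design actually planned, power runs from about 0.94 to about 0.50 across that range. These figures rest on the assumed equation, the stated rates and 25 person-years per cluster; allowing for dropout lowers them by about 0.01 at most.

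The outcome concerned is secondary, and the primary sample size is not touched.

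**What to change.** In Sample size {14}:

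1. Replace the cohort requirement with: 7 clusters (175 individuals) per arm, 350 in total.
2. State the k that was used and its source.
3. Add the power of the planned 10 clusters of 25 per arm as a sensitivity range: about 0.94 at k = 0.25, 0.77 at 0.35, 0.67 at 0.40 and 0.50 at 0.50, with 80% holding up to k of about 0.33. If the value converted from the primary ICC is mentioned, say that it comes from schools and from prevalence in children.

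The cost is a few lines of text and a less favourable power statement at the upper end of the range. Enrolment, conduct and the dropout inflation stay as they are. Cohort follow-up has already ended (Trial status), so the benefit lies in how a null or imprecise cohort result is read.
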